**TRIAL SUMMARY**

| **Trial Title** | **SOLID (Supporting Looked After Children and Care Leavers In Decreasing Drugs, and alcohol):** a pilot feasibility study of interventions to decrease risky substance use (drugs and alcohol) and improve mental health of Looked After Children and Care Leavers aged 12 -20 years |
| --- | --- |
| **Acronym** | SOLID |
| **Summary of Trial Design** | Pilot feasibility randomised controlled trial |
| **Summary of Participant Population** | Looked After Children and Care Leavers (LAC) aged 12-20 years who screen positive for being at risk of early drug and alcohol use (≥ 2 in the CRAFFT). |
| **Planned Sample Size** | Phase 1 Formative Research  20 1:1 interviews with LAC  20 1:1 interviews with Carers  1 focus group with professionals  1 focus group with Drug and alcohol workers  Pre pilot trials  5 1:1 interviews with LAC trialing the interventions  5 1:1 interviews with Drug and Alcohol workers trialing the interventions  LAC leads survey:  Surveys with all named LAC Community Pediatric leads in each local authority in England (n=152).  Intervention finalization workshop  1 focus group with Professionals  1 focus group with LAC and Carers  Phase 2 Pilot RCT  Sample size required - minimum of 35 LAC per arm at follow-up (3 arm trial). Aim to recruit 150 LAC in total to allow for 30% loss to follow-up.  Process Evaluation  20 1:1 interviews with LAC  20 1:1 interviews with Carers  15 1:1 interviews with Drug and alcohol workers  1 focus group with Social Workers  1 focus group with Drug and alcohol workers |
| **Planned Number of Sites** | 5 (Newcastle, Durham and Teesside (Middleborough, Stockton and Redcar) |
| **Intervention Duration** | 6 sessions over a maximum of 12 weeks |
| **Follow Up Duration** | 12 months (+8 week window) |
| **Planned Study Period** | 24 months |

| **Intervention arms** | 2 active intervention arms:   - 6 sessions of Motivational Enhancement Therapy (MET) or - 6 sessions of Social Behavioural Network Therapy (SBNT)   Interventions will take place over a maximum of a 12 week period. |
| --- | --- |
| **Control arm** | Usual social worker delivered care with additional signposting to local drug and alcohol third sector services. |
| **Inclusion criteria** | - LAC aged 12-20 years - Screen positive for at risk of substance misuse i.e. scoring ≥ 2 on the CRAFFT screening questionnaire - Consents to take part in the study |
| **Exclusion criteria** | - Actively receiving treatment from drug and alcohol services - Unable to access drug and alcohol services e.g. due to imminent move out of area. - Unable to give informed consent due to capacity or language barriers |
| **Outcome of pilot feasibility trial** | Stop/Go criteria have been developed for progression to a definitive trial.  Definite Go (‘green light’) defined as :   - ≥60% of eligible participants consenting to pilot feasibility trial; - ≥ 80% LAC attend ≥ 60% of sessions as planned in a given intervention arm. - Retention of ≥ 70% of consented participants for provision of key outcome data at 12 months. - The intervention can be delivered with fidelity i.e. the content, frequency, duration and quality of the intervention can be delivered as set out in the intervention delivery manual. - An indication from qualitative interview and focus group work that the intervention(s) is (are) perceived as acceptable to both young people and Drug and Alcohol workers.   Definite Stop (‘red light’) defined as :   - < 40% of eligible participants consenting to pilot feasibility trial - < 20% LAC attend ≥ 60% of sessions as planned in a given intervention arm. - retention of < 50% of consented participants for provision of key outcome data at 12 months - Value of information analysis shows that future research is not worthwhile (i.e. the expected value of sampling information (EVSI) < £0. - It is clear from the process data from staff and participants that the intervention procedures have low fidelity in terms of content, frequency, duration and quality and that they are unfeasible to deliver. - An indication from qualitative interview and focus group work that the intervention(s) is (are) not acceptable to LAC and Drug and alcohol workers |
| **Primary Outcomes in definitive trial** | - Episodes of heavy episodic drinking (≥5 units in 1 day) in the preceeding 30 day period - Frequency of use of the most problematic classified substance in preceeding 30 days   (data from Timeline Follow-back questionnaire-30) |
| **Secondary Outcomes in definitive trial** | - Self-reported mental health and wellbeing using the Strength and Difficulties Questionnaire (SDQ) and the Warwick-Edinburgh Mental Well-being scale (WEMWBS). - Self-reported health related quality of life measured using the EQ-5D-5L. - Placement stability for the young person - Self-reported occasions of ‘drunkenness’ in the last 30 days (past 30-day intoxication in ESPAD[^7^](#_ENREF_7)) to compare against the objective standard-drink unit measure. - Self-reported sexual behaviour measured using items taken from the computer assisted self-interview (CASI) questionnaire used in the Avon Longitudinal Study of Parents and Children (ALSPAC) supplemented with questions relating to regret in sexual encounters and unprotected sex used in the ESPAD. - Self-reported antisocial and criminal behaviour measured by a questionnaire used in ALSPAC. - Self-reported use of health and social services using a bespoke questionnaire - Estimates of cost to health and social services - Estimates of quality adjusted life years (QALYs) derived from responses to the EQ-5D 5L |
| **Randomisation procedure** | Individual stratified randomisation, via centralised web-based system, based on placement type (residential, not residential), sites, and age band (<14 and ≥14 and over) |
| **Blinding** | Blinding of group allocation will not be possible for the LAC who will complete the self-report follow up assessment.  Where possible the researchers will not know group allocation. |

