**GLOSSARY OF ABREVIATIONS**

| **ABBREVIATION** | **DEFINITION** |
| --- | --- |
| AE | Adverse Event |
| AR | Adverse Reaction |
| AUDIT | Alcohol Use Disorders Identification Test |
| CI | Chief Investigator |
| CRF | Case Report Form |
| CRAFFT | Car, Relax, Alone, Forget, Friends, Trouble(s). |
| DALY | Disability adjusted life year |
| EVSI | Expected value of sampling information |
| ENG | Expected net gain |
| GCP | Good Clinical Practice |
| ICF | Informed Consent Form |
| ISF | Investigator Site File |
| ISRCTN | International Standard Randomised Controlled Trials Number |
| LAC | Looked After Children and Care Leavers |
| MET | Motivational Enhancement Therapy |
| NCTU | Newcastle Clinical Trials Unit |
| NHS | National Health Service |
| NPS | Novel Psychoactive substances |
| OR | Odds ratio |
| PI | Principal Investigator |
| PIC | Participant Identification Centre |
| PIS | Participant Information Sheet |
| QA | Quality Assurance |
| QALY | Quality Adjusted Life Years |
| QC | Quality Control |
| R&D | Research & Development |
| RCT | Randomised Control Trial |
| REC | Research Ethics Committee |
| SAE | Serious Adverse Event |
| SAR | Serious Adverse Reaction |
| SBNT | Social Behavioural Network Therapy |
| SDQ | Strengths and Difficulties Questionnaire |
| SDV | Source Data Verification |
| SOP | Standard Operating Procedure |
| SSI | Site Specific Information |
| USAR | Unexpected Serious Adverse Reaction |
| TLFB-30 | Timeline Follow Back data covering the last 30 days |
| TMG | Trial Management Group |
| TOC | Trial Oversight Committee |
| TMF | Trial Master File |

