### Data Analyses

The initial stage of value of information analysis will be the construction of a mathematical decision model that will synthesise the best available existing evidence from the literature and information from the pilot feasibility trial in order to provide preliminary estimates of effects, costs and cost-effectiveness. Uncertainty around estimates of effects, costs and cost-effectiveness will be accounted for by probabilistic sensitivity analysis and estimated using Monte Carlo simulation, as cost data are unlikely to be normally distributed. Statistical imprecision will be presented as confidence intervals around differences in effectiveness, costs and cost-effectiveness. Threshold sensitivity analyses will be applied to identify the range for costs and effects in which a treatment might need to exist in to be considered cost-effective with respect to standard thresholds for cost-effectiveness (e.g. £20,000 per QALY).

We anticipate that the results of the analysis described above will be insufficient to inform practice because of the amount of uncertainty that surrounds estimates. The VoI analysis will build upon the results of the probabilistic sensitivity analysis to estimate the expected value of sampling information (EVSI). The EVSI will quantify the value of reducing uncertainty via collection of additional data in a definitive trial. Comparing the value of additional information with the financial and opportunity cost to generate the additional information, the expected net gain (ENG) can be calculated as difference between the EVSI and total cost of conducting the further research. The optimal design of a definitive trial will maximise the expected net gain (ENG) to society with regard to sample size. The optimal sample size is that which maximises the difference between EVSI and expected total cost of the research (both the direct cost of the research itself and the opportunity cost of delaying the implementation of a worthwhile intervention whilst research is on-going). The estimated optimal sample size will be inflated according to the rate of missing data in the trial data to achieve the optimal sample size of complete data cases and to determine the final sample size for a definitive trial.

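### The value-of-information red light (EVSI below £0) can never be met, so the only economic stop/go criterion has no effect

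*Protocol*

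**What the plan says.** The fourth of the six red-light criteria in the Trial Summary (Outcome of pilot feasibility trial) is that the value-of-information analysis finds further research not worth doing, which it defines as "the expected value of sampling information (EVSI) < £0". None of the five green-light criteria is economic; they cover consent, attendance, retention, fidelity and acceptability. The other five red-light criteria cover the same five topics. This bullet is therefore the only place where economics enters the stop/go scheme.

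Section 11.2.2 (Data Analyses) says what EVSI means: "The EVSI will quantify the value of reducing uncertainty via collection of additional data in a definitive trial". Cost is brought in separately, where "the expected net gain (ENG) can be calculated as difference between the EVSI and total cost of conducting the further research". The cost side comprises "both the direct cost of the research itself and the opportunity cost of delaying the implementation of a worthwhile intervention whilst research is on-going". ENG is then used for design: "The optimal design of a definitive trial will maximise the expected net gain (ENG) to society with regard to sample size". The Glossary also keeps the two apart, with "Expected net gain" as its own entry beside EVSI. Nowhere is EVSI redefined as net of cost, and no other value-of-information stop rule is given.

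**The concern.** The words introducing the bullet have a clear purpose: stop if a further trial would not repay what it costs. The definition attached to them tests something else. It asks whether the information has negative value before any cost is counted, and information that a decision-maker is free to ignore cannot have negative value.

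Objective 5 of Phase 2 (section 3.2) is to apply the stop/go criteria as pre-specified. Applied literally, this one is passed whatever the data show. A definitive trial costing many times the value of what it could teach would not trip it. Section 11.2.2 itself expects the estimates after the pilot to be very uncertain, and that tends to make EVSI clearly positive. Replacing the threshold once the pilot's results are known would lose the benefit of having set it beforehand.

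**Working it through.** The plan gives a threshold here and no numerical result, so there is no figure to reproduce. The check is whether the threshold can be crossed.

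**1. General result.** Let NB_d be the net benefit of option d (MET, SBNT or usual care) and X the data from a definitive trial. Then

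EVSI = E_X[ max_d E(NB_d | X) ] - max_d E(NB_d).

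Let d* be the option that looks best now. For every X, max_d E(NB_d | X) is at least E(NB_d* | X). Averaging over X, the first term of EVSI is at least E(NB_d*), which is the second term. Hence EVSI >= 0 for any prior, number of arms and sample size (Jensen's inequality). Equality holds when no possible data would change the choice. Even then the strict inequality in the bullet is not met.

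**2. Two options, normal model.** With prior mean incremental net benefit m and pre-posterior standard deviation s, and k = |m|/s,

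EVSI per person = s × [φ(k) - k × Φ(-k)].

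Taking s = £1,000 (assumed):

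| m | k | EVSI per person |
|---|---|---|
| £0 | 0 | £399 |
| -£1,000 | 1 | £83 |
| -£5,000 | 5 | about £0.00005 |

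The value falls towards zero as the case weakens but does not cross it.

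**3. Wider numerical check.** The same formula was evaluated over 7 prior means (-£3,000 to £3,000), 4 prior SDs (£100 to £1,000), 3 individual SDs (£2,000 to £10,000) and 4 sample sizes (50 to 600 per arm), which is 7 × 4 × 3 × 4 = 336 settings. The minimum was £0.0. Across 200 random three-option settings by simulation the minimum was -1.7 × 10^-11, which is floating-point rounding of zero.

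**4. Contrast with ENG as section 11.2.2 defines it.** All inputs are assumed, because the protocol gives none: prior SD £500, individual SD £5,000, n = 300 per arm, total research cost £1.5m.

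s = √[500^4 / (500^2 + 2 × 5,000^2 / 300)] = √150,000 = £387.3.

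At m = £0, EVSI per person = 387.3 × 0.3989 = £154.51. For 20,000 beneficiaries this is £3.09m, and ENG = 3.09 - 1.50 = +£1.59m. The same steps give:

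| m | Beneficiaries | EVSI per person | Population EVSI | ENG | EVSI < £0? | ENG <= £0? |
|---|---|---|---|---|---|---|
| £0 | 20,000 | £154.51 | £3.09m | +£1.59m | no | no |
| £0 | 2,000 | £154.51 | £0.31m | -£1.19m | no | yes |
| -£300 | 20,000 | £48.68 | £0.97m | -£0.53m | no | yes |
| -£3,000 | 20,000 | about £0 | about £0 | -£1.50m | no | yes |

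At this one sample size, ENG separates the cases and EVSI does not.

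**The case against.** Several points can fairly be made for the plan.

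- The intention is plain from the bullet's opening words, and section 11.2.2 will compare EVSI with research cost and report ENG in any case, so a negative ENG would be visible to those deciding. This stands as mitigation. It does not make the stated criterion work, because the definition attached to it is what would be applied.
- The pilot's primary outcomes (section 3.3) are recruitment, retention, acceptability and engagement. Value of information is a secondary objective, and section 11.1 presents it as additional evidence. This also stands. It limits the consequence to one of six red-light criteria, and no participant, data item or pilot estimate is affected.
- An ENG rule works only once the beneficiary population, time horizon and cost-effectiveness threshold are set. Section 11.2.2 gives the threshold only by example (£20,000 per QALY), and its closing paragraph treats the number who might benefit and the period of use as uncertain. This stands and shapes the fix.

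Two stronger readings are tempting but not supported.

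- A reader might infer that the protocol names ENG as its stop/go quantity and then fails to use it. It does not. Section 11.2.2 uses ENG to choose the definitive trial's sample size. ENG is the natural repair because it is the only quantity in the protocol that sets the value of research against its cost.
- A reader might also infer that the optimal sample size is miscalculated, because "The estimated optimal sample size will be inflated according to the rate of missing data in the trial data" only after the optimum is found. The text does not establish this. The step is meant to deliver the optimal number of complete cases, and the protocol does not say that the cost function leaves out recruits who are later lost. With c the cost per recruit and q the missing rate, pricing each complete case at c/(1 - q), maximising over complete cases and then dividing by (1 - q) gives the same answer as maximising over recruits. How the cost function is specified can reasonably be left to a later analysis plan.

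**Conclusion.** Wrong as written. Under the protocol's own definition of EVSI the criterion has probability zero of being met, and only Monte Carlo noise around a true value at or near zero could produce a negative estimate. This is a mathematical property of EVSI and rests on no assumed input; the monetary figures above only illustrate it. The practical effect is that the stop/go scheme contains no working economic test. It does not follow that the scheme as a whole fails: the remaining five red-light criteria operate as stated.

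**What to change.** Replace the value-of-information bullet in the Trial Summary with: the expected net gain (ENG: population EVSI minus the total cost of the further research, including the opportunity cost of delay, as in section 11.2.2) is at or below £0 at every sample size considered.

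Before the pilot results are seen, state the cost-effectiveness threshold, beneficiary population, time horizon and range of sample sizes to be used for this test, and report how the conclusion changes when they are varied.

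The cost is a short change of wording plus agreement on those inputs; no extra data are needed, since ENG is already planned. The drawback is that the rule then depends on assumptions which the protocol itself regards as uncertain, and a different choice of population or horizon could reverse the result. That is why they should be fixed in advance and the sensitivity results shown.

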**GLOSSARY OF ABREVIATIONS**

| **ABBREVIATION** | **DEFINITION** |
| --- | --- |
| AE | Adverse Event |
| AR | Adverse Reaction |
| AUDIT | Alcohol Use Disorders Identification Test |
| CI | Chief Investigator |
| CRF | Case Report Form |
| CRAFFT | Car, Relax, Alone, Forget, Friends, Trouble(s). |
| DALY | Disability adjusted life year |
| EVSI | Expected value of sampling information |
| ENG | Expected net gain |
| GCP | Good Clinical Practice |
| ICF | Informed Consent Form |
| ISF | Investigator Site File |
| ISRCTN | International Standard Randomised Controlled Trials Number |
| LAC | Looked After Children and Care Leavers |
| MET | Motivational Enhancement Therapy |
| NCTU | Newcastle Clinical Trials Unit |
| NHS | National Health Service |
| NPS | Novel Psychoactive substances |
| OR | Odds ratio |
| PI | Principal Investigator |
| PIC | Participant Identification Centre |
| PIS | Participant Information Sheet |
| QA | Quality Assurance |
| QALY | Quality Adjusted Life Years |
| QC | Quality Control |
| R&D | Research & Development |
| RCT | Randomised Control Trial |
| REC | Research Ethics Committee |
| SAE | Serious Adverse Event |
| SAR | Serious Adverse Reaction |
| SBNT | Social Behavioural Network Therapy |
| SDQ | Strengths and Difficulties Questionnaire |
| SDV | Source Data Verification |
| SOP | Standard Operating Procedure |
| SSI | Site Specific Information |
| USAR | Unexpected Serious Adverse Reaction |
| TLFB-30 | Timeline Follow Back data covering the last 30 days |
| TMG | Trial Management Group |
| TOC | Trial Oversight Committee |
| TMF | Trial Master File |

# BACKGROUND

## The Importance of Substance Use in Looked After Children and Care Leavers (LAC)

Drug and alcohol (substance) use in young people is a major public health problem, which causes a significant economic strain on the NHS and society.[^1^](#_ENREF_1) Substance use accounts for 11% of the total burden of disease, calculated as disability adjusted life years lost, in high income countries.[^2^](#_ENREF_2) It was estimated in 2013 that alcohol related harm costs the UK £21 billion annually with an additional £15.4 billion estimated to result from drug addiction.[^3^](#_ENREF_3) Risky substance use in adolescence predicts adult alcohol and drug use and significantly increases the risk of adult mental health disorders, crime and poverty.[^4-6^](#_ENREF_4) Although there has been an overall fall in drug use in teenagers over the last decade, the UK is still in the top five for lifetime use of cannabis and other illicit drugs in 15 to 16 year olds and the top ten with regards to binge drinking (heavy sessional or risky single occasion drinking) in the last 30 days across 36 European countries.[^7^](#_ENREF_7) In addition to cannabis use, there has been an explosion in the use of novel psychoactive substances (NPS) in the UK, commonly known as ‘legal highs’, which are likely to have significant physical and mental health consequences.[^8^](#_ENREF_8)^,^ [^9^](#_ENREF_9)

In 2014, one in every 200 children and young people (CYP) in England, a total of 69,000, were looked after by local authority services, a rise of 7% in 5 years.[^10^](#_ENREF_10) Looked After Children and Care Leavers (LAC) are those children and young people up to the age of 21 who have been placed under the legal care of local authorities. The 2014 NICE guidelines, ‘Interventions to reduce substance misuse among vulnerable young people’, highlighted LAC as a vulnerable group to substance use.[^11^](#_ENREF_11) About 7% of the approximately 21,000 young people accessing specialist drug and alcohol services self-reported that they were in care.[^12^](#_ENREF_12) Unfortunately, there is limited research, including cost effectiveness data, and, at present no national guidelines, on the most effective interventions to decrease risky drug and alcohol use in this group. This lack of data was highlighted by the CMO’s annual report 2012, which stated that one of the key research areas was to assess the most effective interventions to reduce multiple risk taking behaviour, including drug and alcohol use in this group.[^13^](#_ENREF_13) LAC have multiple risk factors for substance use, poor mental health, school failure and early parenthood.[^14^](#_ENREF_14) These factors include parental poverty, absence of support networks, parental substance misuse, poor maternal mental health, early family disruption and, in the majority of cases, abuse and/or neglect.[^15^](#_ENREF_15)^,^ [^16^](#_ENREF_16) LAC, aged 11 to 19 years, have a 4 fold increased risk of drug and alcohol use than children not in care.[^17^](#_ENREF_17) Twenty-five percent of LAC aged 11 to 19 years and 42% of young people in residential care drank alcohol at least once a month, compared to 9% of young people not looked after.[^17^](#_ENREF_17) A national survey of care leavers showed that 32% smoked marijuana daily and data from 2012 showed 11.3% of LAC aged 16-19 years had a diagnosed substance use problem.[^18^](#_ENREF_18)^,^ [^19^](#_ENREF_19) In addition, LAC have a nearly fivefold increased odds of at least one mental health diagnosis including anxiety, depression or behavioural disorders (OR: 4.92; 95% CI: 4.13, 5.85) than their non-LAC peers, further increasing their risk of substance misuse and poor life chances.[^20^](#_ENREF_20)

The long term outcome of LAC in terms of health, education, employment and risk of criminality is poor, resulting in a significant cost to society and increased risk of intergenerational poverty. Forty percent of 20 year olds who have been in the care system are not in education, employment or training (NEET).[^19^](#_ENREF_19) Data from the 1960 British birth cohort at age 30 years showed that men with a history of being in public care were twice as likely to be unemployed (OR: 2.6; 95% CI: 1.4, 5.0), have a criminal conviction (OR: 2.3; 95% CI: 1.5, 3.4) and have been seen for a mental health, drug or alcohol related problem after the age of 16 years (OR: 1.7; 95%CI: 1.1, 2.6) than non-looked after peers.[^21^](#_ENREF_21) There are limited longitudinal data looking at the impact of drug and alcohol use on young people as they transition to adulthood. However, research from the criminal justice system in Scotland showed that 34% of youth offenders had been in care. Of these offenders, 75% reported drug usage (compared to 57% of those not previously in care).[^22^](#_ENREF_22) Effective interventions in LAC could have a beneficial effect on the long term mental and physical health of these vulnerable young people, importantly reduce health inequality and, due to their increased risk of early parenthood, potentially impact intergenerational health.

